### Objectives

This protocol describes a randomized controlled trial that aims to test the efficacy of a fully automated mobile phone–based intervention on positive mental health among university students. The primary hypothesis is that participants in the intervention group will report significantly higher positive mental health (measured by the primary outcome measure) at follow-up compared with participants in the control group. Secondary hypotheses are that the intervention group will report significantly higher emotional, social, and psychological well-being as well as significantly lower rates of anxiety and depression symptomatology (measured by primary and secondary outcomes) at follow-ups compared with participants in the control group. These hypotheses are proposed at 3-, 6-, and 12-month follow-ups. Positive emotions and thoughts are hypothesized to mediate the relationship between access to the intervention and outcomes.

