### Outcomes and Measures

A baseline questionnaire will investigate demographic data (age, gender, and social status), primary outcome [2], and secondary outcomes [29]. Follow-up questionnaires will investigate primary and secondary outcomes. Outcomes will be investigated at baseline and at 3, 6, and 12 months after randomization. Participants will receive and complete questionnaires through their mobile phones.

Primary outcome will be positive mental health, assessed with the 14-item Mental Health Continuum Short Form (MHC-SF) [2]. Higher scores indicate greater emotional, social, and psychological well-being (range 0-84). Secondary outcomes will be depression and anxiety symptomatology assessed as the score on corresponding subscales of the Hospital Anxiety Depression Scale (HADS) [29].

To investigate mediators of the intervention [20], 2 face-valid items will measure the frequency of positive thoughts (‘‘During the last week, to what extent have you experienced positive thoughts” and “During the last week, to what extent have you experienced positive emotions”). Items will be rated on a scale ranging from 0= *not at all* to 9= *to a very high extent*. Mediators are assessed at baseline, midintervention (end of week 5), and at subsequent follow-ups. Mediation scores are hypothesized to be significantly higher in the intervention group compared with the control group.

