### Statistical Methods

All analyses will be done under the intention-to-treat principle, where all randomized individuals will be included. Missing outcome data will initially be handled by a complete-case analysis, which assumes that data are missing at random. If data are systematically missing, then it may be the case that early responders differ from late responders, and in extension that late responders are more similar to nonresponders. We will, therefore, explore the plausibility of the missing at random assumption by regressing the primary outcomes on the number of follow-up attempts needed before a response was recorded. To further explore the missing at random assumption, attrition will be investigated among study groups by comparing baseline characteristics between those who did and did not respond at follow-up.

For all models, coefficients of interest will be assessed for statistical significance using a null hypothesis testing approach, where tests will be 2-tailed at the .05 significance level. Alongside the null hypothesis tests, posterior distributions using a Bayesian approach will be calculated for each coefficient. Both significance tests and posterior distributions will create a basis for scientific inference [34].

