**Figure 1 figure1:**
[figure not shown]
Flowchart of the recruitment procedure.

The primary outcome (MHC-SF total score) is a discrete measure, which may be skewed; thus, we will regress this outcome on group allocation using negative binomial regression. Both unadjusted and adjusted models will be explored (adjusting for demographics, total MHC-SF, and mediator variables at baseline).

The 3 subscales of MHC-SF (emotional well-being, social well-being, and psychological well-being) are mean scores from Likert scale items, which should, because of the law of large numbers, tend toward normality. If by visual inspection it is deemed that the measures are skewed, we will use log transformation. We will regress the individual scores against group allocation using normal linear regression. Both unadjusted and adjusted models will be explored (adjusting for demographics and each score, respectively, and mediator variables at baseline).

Depression and anxiety scores from HADS will also be regressed against group allocation using negative binomial regression. Both unadjusted and adjusted models will be explored (adjusting for demographics, depression, and anxiety, respectively, and mediator variables at baseline).

Mediators will be explored using a causal inference framework, where Monte Carlo methods are relied upon for inference. A total of 3 models will be created for each outcome measure: 2 that investigate the mediating factors on their own and a third model that incorporates all mediators at once.

Effect modification tests will be performed in all models to assess if any of the baseline characteristics moderate the effect of the intervention. Adjusted models will be primary.

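### Effect modification is to be tested for any baseline characteristic in all models at two-sided .05, with no multiplicity control or exploratory label, so false moderators are likely

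*Protocol article*

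**What the plan says.** All references are to the protocol article.

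- **Scope.** Statistical Methods, closing paragraph: "Effect modification tests will be performed in all models to assess if any of the baseline characteristics moderate the effect of the intervention". Neither the outcomes nor the time points are restricted, and no moderator is named.
- **Threshold.** Statistical Methods, second paragraph, which covers every model: "coefficients of interest will be assessed for statistical significance using a null hypothesis testing approach, where tests will be 2-tailed at the .05 significance level". In an effect modification test the coefficient of interest is the interaction, so this level applies to it.
- **Second basis for inference.** Posterior distributions are to be reported beside the tests, and both are to inform the conclusions. No posterior threshold and no shrinkage prior is given.
- **Outcomes.** Models are planned for the MHC-SF total, its three subscales and the two HADS scores.
- **Follow-ups.** Objectives: "These hypotheses are proposed at 3-, 6-, and 12-month follow-ups".
- **Candidate characteristics.** Outcomes and Measures: "A baseline questionnaire will investigate demographic data (age, gender, and social status), primary outcome [2], and secondary outcomes [29". The two mediator items are also measured at baseline. The adjusted model for the primary outcome is described as "adjusting for demographics, total MHC-SF, and mediator variables at baseline", and the other adjusted models follow the same pattern with their own baseline score.

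**The concern.** Taken together, the two sentences in Statistical Methods fix both how widely moderation is searched for and the level at which each search is judged. A 5% test repeated over many characteristics, outcomes and follow-ups will produce nominally significant interactions when the intervention works equally for everyone. No outcome, follow-up or moderator has priority, so nothing in the article separates a chance interaction from a real one.

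At stake is what the trial may say about for whom the programme works. The Introduction presents a model in which individual factors moderate the effect of positive practice. A chance moderator could therefore be read as support for the programme's own theory.

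**Working it through.** **The plan's own figure.** For a standardised effect of 0.3, 80% power and two-sided .05, the normal approximation gives 2 × (1.960 + 0.842)² / 0.3² = 174.4, so 175 per arm. The t-based calculation gives 175.4, so 176 per arm and 352 in total, as stated. Then 352 / 0.70 = 502.9, so 503, also as stated. The article gives no count or error rate for the moderator tests.

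**Counting the tests** (adjusted models only, which the plan makes primary)

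- Outcomes: 1 (MHC-SF total) + 3 (subscales) + 2 (HADS) = 6.
- Follow-ups: 3. The Objectives attach these to the main hypotheses. They carry over to moderation because the tests are planned in all models.
- Models: 6 × 3 = 18.
- Characteristics per model: 3 demographics + 1 baseline score + 2 mediator items = 6. This is inferred from the adjustment sets.
- Single-interaction tests: 18 × 6 = 108.

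Unadjusted and mediation models are not counted; including them could only raise the rates.

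**Formulas.** With k independent null tests, P(at least one p < .05) = 1 − 0.95^k. The expected number of false positives is 0.05 × k, whatever the correlation.

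**Correlated tests.** The article gives no correlations, so values of 0.3, 0.6 and 0.8 between outcomes and between follow-ups were assumed. Null trials were simulated with 352 participants, simple 1:1 allocation and linear models (used for speed in place of negative binomial), 1,500 trials per setting.

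| Reading of the plan | Tests k | Independent | Correlation 0.3 / 0.6 / 0.8 | Expected false positives |
|---|---|---|---|---|
| 6 characteristics, all 18 models | 108 | 99.6% | 99% / 93% / 80% | 5.4 |
| 3 demographics only, all 18 models | 54 | 93.7% | 91% / 78% / 59% | 2.7 |
| 6 characteristics, 6 outcomes, one follow-up | 36 | 84.2% | 79% / 67% / 55% | 1.8 |
| 6 characteristics, MHC-SF total, 3 follow-ups | 18 | 60.3% | 55% / 50% / 42% | 0.9 |
| 6 characteristics, one model | 6 | 26.5% | about 25% | 0.3 |
| One joint 6-df test in each of 18 models | 18 | 60.3% | 58% / 40% / 28% | 0.9 |
| One joint 6-df test, MHC-SF total, 3 follow-ups | 3 | 14.3% | 15% / 11% / 10% | 0.15 |

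**Sensitivity.** A second simulation built the MHC-SF total from its subscales, with assumed correlations of 0.3–0.7. It gave 90–97% for six characteristics in all models, 68–85% for demographics only, and 47–53% for the primary outcome at three follow-ups. Counting the baseline MHC-SF score and both HADS scores in every model makes eight characteristics and 144 tests: 94–99%, with 7.2 false positives expected. At an extreme uniform correlation of 0.9 the six-characteristic family falls to about 60–64%.

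**Power for a real moderator.** With 352 analysed, the main-effect standard error is 2/√352 = 0.107 SD. For a balanced binary moderator the interaction's standard error is twice that, 0.213. An interaction of 0.3 then has z = 0.3/0.213 = 1.41 and power of about P(Z > 1.96 − 1.41) = 29%. Chance moderators would be frequent, while a real one of that size would usually be missed.

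**The case against.** The strongest reply is that the size of the problem rests on details the article leaves open.

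- **No decision rule is stated.** A reader might infer that a single p < .05 in any one model declares a moderator. The article does not say so, and it also names posterior distributions as a basis for inference. This stands as a limit on the claim. It does not remove the concern: with no threshold or shrinkage prior stated, the posteriors are not shown to control the error.
- **The form of the test is open.** Asking whether any characteristic moderates the effect could also describe one joint test per model. That stands, and it lowers the figures considerably. Over the 18 models they are still 28–58%.
- **The count of six and the correlations are not in the text.** Also true, which is why ranges are shown. Expecting 5.4 of 108 null tests to fall below .05 is simply the nominal rate per test.
- **Moderation is not among the stated hypotheses, and test form and multiplicity handling often sit in an analysis plan that is not shown.** Mere silence would be no finding. Here, however, the article states the scope (all models) and the level (.05 for all models). An analysis plan that controlled the error would have to narrow or override those sentences. The article says that adjusted and unadjusted models and the mediators will be explored, but it does not set the moderator tests apart from significance testing.

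A reader might also infer that moderator results will decide who is offered the programme. Nothing in the article says that.

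**Conclusion.** The concern holds as a defect in the planned moderator analyses, and it should be corrected before analysis. Run as written, with tests in all models at .05, these analyses exceed a 5% chance of at least one false moderator on every reading checked. The chance is roughly 80–99% for about 108 single-interaction tests under assumed correlations of 0.8 down to 0.3, and about 60–90% with demographics only. It is about 42–60% for the primary outcome at three follow-ups, about 25% for one model, and about 28–58% with one joint test in each of the 18 models.

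It would go too far to say that the plan almost always finds a spurious moderator. That fits only the full family of single tests, and even there not at very high correlations. It would also be wrong to read this as inflating the type I error of the main treatment comparison, which these tests do not touch. The figures rest on the inferred list of six characteristics, on assumed correlations and on linear models.

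**What to change.** Replace the effect modification sentence in Statistical Methods with text to this effect:

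*Effect modification will be tested for significance only for the MHC-SF total score at one follow-up named in advance, in the adjusted model, by one joint test of all treatment-by-baseline interactions at two-sided .05. Individual moderators will be examined by Holm-adjusted tests only if the joint test is significant. Interactions for all other outcomes and follow-ups will be reported as estimates with intervals, labelled exploratory, without significance claims.*

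The list of baseline characteristics in the joint test should be stated in the same place. When there is no moderation, the chance of a moderator claim is then at most about 5%.

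The change costs a few sentences and needs no new data or participants. All estimates can still be reported. The price is lower power to declare any single moderator significant: after the joint test, the smallest of six p-values must fall below 0.05/6 = 0.0083. Other gatekeeping schemes would also serve, provided significance claims are confined to a small family fixed in advance.

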### Ethical Statement

The study has received ethical approval from the Regional Ethical Review Board, Linköping University, Sweden (Dnr 2018/519-32).

## Results

Data will be collected between autumn 2018 and spring 2019. Results are expected to be published in 2020.

## Discussion

### Overview

This paper describes the design of a study that will evaluate the effect of a mobile phone–based intervention to increase positive mental health among university students. This study will add knowledge to the efficacy of a fully automated PPI. Previous research has investigated partly digital interventions and often only included single component interventions.

### Strengths and Limitations

A potential challenge could be recruiting sufficient number of participants. According to our power analysis, we need just above 500 participants to achieve 80% power. By including some of the larger universities in Sweden and setting the recruitment period to 6 months, we believe that the study will recruit a sufficient sample.

A strength of the study is that it will investigate potential mechanisms of change. The proposed mediators in the study (positive emotions and cognitions) are based on a framework of mechanisms of positive interventions (the positivity-activity model). However, the challenge is how to measure these mediators in a reliable and feasible way. In a randomized controlled trial with already comprehensive baseline and follow-up questionnaires, it was not realistic to include lengthy validated instruments of, for example, positive emotions. A total of 2 single face valid items were therefore used to measure proposed mediators.

Another strength of the study is the use of the MHC-SF [2] to measure positive mental health. It is a validated comprehensive instrument including emotional and social well-being as well as psychological function. Positive mental health is a complex construct that requires the use of an instrument that captures both the hedonic and eudaimonic dimensions of well-being.

### Conclusions

The promotion of positive mental health among the general population is increasingly becoming a core component of the public mental health agenda in Europe [17]. Mobile phone–based interventions could be a cost-effective choice for mental health promotion and an effective way to disseminate evidence-based interventions to larger audiences. However, more rigorous and larger studies that can clarify the evidence base in this area are needed [27]. This protocol describes a randomized controlled trial investigating a newly developed, fully automated, mobile phone–based intervention promoting well-being among university students. The trial can contribute to the knowledge on the feasibility and effect of the mobile phone–based intervention in promoting mental health.

## Abbreviations

e-resource: electronic resource
HADS: Hospital Anxiety Depression Scale
MHC-SF: Mental Health Continuum Short Form
PPI: positive psychology intervention
SMS: short message service
